#### Study Intervention Delivery and Assessment

After randomization, participants will gain access to Anathema either via the co-developed app (older adults in the Netherlands, and colorectal cancer and stroke survivors in Portugal) or the Instahelp platform (older adults in Austria). At this stage, the 3 abovementioned service models will be tested for acceptability, feasibility, and preliminary efficacy.

The self-guided model will be tested with older adults in the Netherlands. Participants will gain access to the treatment modules every week, being prompted to complete the modules in approximately 1 week. If participants fail to complete the modules in the specified time frame, a reminder will be sent. Upon completion, participants will receive access to the following module. The preliminary efficacy of the intervention will be assessed at midtest (T2) and after the completion of the program at posttest (T3), using the measures listed above.

The guided model will be trialed by colorectal cancer and stroke survivors in Portugal. Participants will gain access to the intervention after a preliminary online or telephone appointment is conducted with their assigned study psychologist. This first e-appointment aims to discuss the program’s structure, report the baseline findings, and tailor the intervention according to participants’ needs and preferences. Once clinical psychologists and participants reach an agreement, the selected modules will be prescribed and made available weekly to the participants. Participants will be prompted to complete the modules in approximately 1 week. Within 24 hours of module completion, the study psychologists, based on the reported outcomes, will assess participants’ progress and determine whether it is appropriate or not for the participants to proceed to the next module. If so, participants will receive access to the following module. If not, study psychologists will instruct participants on what needs to be completed to advance to the next module. The preliminary efficacy of the intervention will be assessed at midtest (T2) and after the completion of the program at posttest (T3), using the measures listed above.

The blended model will be assessed by older adults in Austria. Participants will gain access to the intervention after a preliminary 60-minute videoconference appointment is conducted with their assigned study psychologist. This first appointment aims to discuss the program’s structure and tailor the intervention according to participants’ needs and preferences. Once clinical psychologists and participants reach an agreement, the selected modules will be prescribed and made available every week to the participants. Participants will be prompted to complete the modules weekly. Within 24 hours of module completion, the study psychologists, based on the reported outcomes, will assess participants’ progress and determine whether it is appropriate or not for the participants to proceed to the next module. If so, the participants will receive access to the subsequent module. If not, clinical psychologists will instruct participants on what needs to be completed to advance to the next module. Online videoconference appointments will be conducted at the onset of the program (session 1), at week 3/4 (session 2), and at the end of the program (session 3) to blend self-care work and asynchronous support with therapeutic videoconference synchronous support. During the videoconference appointments, study psychologists will assess participants’ progress, instruct participants on how to implement treatment strategies, and determine whether it is appropriate or not for participants to proceed with the program. Upon request, sessions are also possible for participants requiring additional support from clinical psychologists. Still, they are limited to 5 extra sessions, at a maximum of 1 per week and for approximately 40 to 50 minutes. If an extra videoconference session is requested, it will replace the scheduled asynchronous session to avoid redundancy. The preliminary efficacy of the intervention will be assessed at midtest (T2) and after the completion of the program at posttest (T3), using the measures listed above (Table 3).

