**Figure 2 figure2:**
[figure not shown]
Anathema app overview.

The program was created using a participatory design approach [40], involving its primary (older adults, colorectal cancer survivors, and stroke survivors), secondary (psychologists and sexologists), and tertiary end users (managers of care homes, day-care centers, or clinics). Anathema’s development followed an agile development framework [41] and was based on peer-review sources (eg, [12,42-49]) and user research insights (eg, [37]). The program adopts a transdiagnostic structure, featuring sexual health promotion strategies considered appropriate for the different populations under study. Its central components are psychoeducation, cognitive restructuring, mindfulness, communication skills training, exercises to promote sexual sensation awareness and erotic repertoire, and masturbatory and sensate focus exercises. Anathema is structured into 5 modules to be completed for up to 8 weeks. A detailed description of Anathema’s structure and content is provided in Table 1.

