Regarding human support, Anathema may be delivered using 3 service models. The subtypes are as follows: unguided or self-guided (the primary end user follows all the intervention programs on her/his own with no support from a clinical psychologist), guided (the intervention program incorporates clinical psychologists’ synchronous or asynchronous support, guidance, and feedback via email, chat, etc), and blended (treatment programs that combine face-to-face or videoconference sessions with online treatment modules in an integrated and sequential format). An iOS/Android app co-developed in the context of this project will be used to deliver the self-guided version of the intervention to older adults in the Netherlands. In this approach, no clinical psychologist-participant contact is foreseen. This app will also guide colorectal cancer and stroke survivors throughout the program in Portugal. Synchronous (eg, voice and chat) and asynchronous (eg, email) communication channels will be available to provide participants with guidance and support weekly and upon request. The blended-care format intervention will be delivered to older adults in Austria via an iFrame to be made available on the Instahelp platform [50]. In this case, the developed modules will be combined with 3 videoconference sessions (at the onset, mid, and conclusion of the intervention) focusing on the clarification of the intervention’s content and strategies to be implemented. Upon request, sessions are also possible for participants requiring additional support from clinical psychologists.

In this research, TAU refers to the routine sexual health care participants would receive at the recruitment sites. Therefore, the type of TAU received may vary and include pharmacologic treatment or psychosocial support. WLC participants will be informed that they are free to access any form of support during the study and encouraged to seek professional help in case they experience symptomatic deterioration or other difficulties. WLC participants will be offered the same treatment protocol applied to the experimental group after completion of the program (approximately 8 weeks from baseline).

**Table 1 table1:** Anathema’s structure and content.

Module	Intervention components	Content

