Let’s talk about sexuality? (week 1)	Psychoeducation	Concepts underlying sexuality Male and female anatomies and erogenous zones Sexual response and sexual pleasure Sexual health, sexual rights, and their importance Activities: Setting my personal goals within Anathema, and I get pleasure from…
When aging and illness come in the way (week 2)	Psychoeducation (tailored to each study population)	Successful aging Sexual expression in older age Physiological, cognitive, and emotional changes in older age Sexual problems and sexual dysfunction in older age Biopsychosocial changes associated with colorectal cancer (CRC) and stroke, and their impact on survivors’ sexual health Activities: Practicing self-compassion, and identifying and classifying the changes I experience in my sexual life due to aging, CRC, or stroke
Emotional and physical intimacy (weeks 3-6)	Psychoeducation Cognitive restructuring Mindfulness Communication skills training Sensate focus	Sexual beliefs, thoughts, and emotions, and their impact on sexuality Identifying, evaluating, and modifying maladaptive thinking Interpersonal relationship and communication issues commonly associated with aging, CRC, and stroke Restoring interpersonal relationships and intimacy Activities: Rational disputation, diary of thoughts and emotions, practicing mindfulness, identifying and overcoming relationship stressors, improving communication, and sensate focus
Exploring one’s sexuality (week 7)	Psychoeducation Mindfulness exercises Sexual skills training	Giving and receiving pleasure: eroticism, masturbation, and intercourse Sex aids and strategies to enhance sexual pleasure and satisfaction Activities: Practicing mindfulness and identifying treatment options
Planning for a long-term fulfilling sex life (week 8)	Relapse prevention	Overview of Anathema and progress evaluation Strategies to maintain progress and prevent setbacks Promotion of a healthy lifestyle as key to better sexual health Activities: Managing therapeutic progress, and strategies to enhance sexual pleasure and satisfaction

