#### Enrollment and Randomization

Participants fulfilling all eligibility criteria will be registered and randomized. Simple randomization will be performed by an independent statistician, using a computerized program. Older adults in Austria, and colorectal cancer and stroke survivors in Portugal will be submitted to subsequent simple randomization so that they are randomly assigned to one of the study psychologists. Colorectal and stroke survivors will be guided by study psychologists from SexLab, and older adults in Austria will have access to blended support provided by clinical psychologists from Instahelp. Older adults in the Netherlands will not be submitted to this second randomization procedure, given that they will get access to the self-guided version of the program. Participants randomized to Arm A (experimental condition) will receive immediate access to Anathema. Participants assigned to the WLC condition will gain access to the program approximately 8 weeks after randomization and after being submitted to a second baseline assessment to confirm their eligibility for the study.

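### Posttest is tied to finishing the program, while controls are re-assessed and cross over about 8 weeks after randomization; one calendar schedule from randomization should apply to both arms

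*Protocol article*

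**What the plan says.** All references are to the protocol article.

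- **Anathema arm, posttest.** Study Intervention Delivery and Assessment says, for the self-guided, guided and blended models alike: "The preliminary efficacy of the intervention will be assessed at midtest (T2) and after the completion of the program at posttest (T3". The text gives no week and no window.
- **Anathema arm, pace.** The same section opens each module only once the previous one is done. In the guided and blended models a psychologist also reviews progress within 24 hours and decides whether the participant moves on. In those two models access starts only after a preliminary appointment, with no time limit given, although Enrollment and Randomization promises Arm A immediate access.
- **Control arm.** Enrollment and Randomization says: "Participants assigned to the WLC condition will gain access to the program approximately 8 weeks after randomization". Before that comes a "second baseline assessment to confirm their eligibility for the study". Study Intervention and TAU puts the offer to controls "after completion of the program (approximately 8 weeks from baseline", so the anchor is randomization in one place and baseline in the other.
- **Planned length.** "Anathema is structured into 5 modules to be completed for up to 8 weeks". The last row of Table 1 is "Planning for a long-term fulfilling sex life (week 8".
- **Analysis.** The Analysis section specifies intention to treat with mixed models for the secondary (efficacy) outcomes.

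**The concern.** A between-group comparison of outcomes that may change over time needs both arms measured at the same distance from randomization, while the controls are still untreated. Here one arm's measurement waits for an event that depends on the participant's own progress, and the other arm runs on the calendar.

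Two things can follow. A slow Anathema participant may reach posttest when the controls already have the program, so no concurrent untreated comparison exists. A participant who stalls without withdrawing never meets the stated trigger, and the text gives no other posttest time for that person. Stalling may well be related to lack of benefit. An intention-to-treat analysis cannot restore a measurement that was never scheduled.

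The efficacy results are preliminary, but they have a use: Study Design says the pilots will estimate sample sizes for the parent trials and give a preliminary evaluation of between-group differences.

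**Working it through.** **Step 1. Reproduce the planned length.** Inputs are the module weeks in Table 1: week 1, week 2, weeks 3-6, week 7 and week 8.

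1 + 1 + 4 + 1 + 1 = 8 weeks over 5 modules. This matches the stated 8 weeks.

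**Step 2. Compare with the control clock.** Controls gain access at about 8 weeks. Slack = 8 - 8 = 0 weeks. The arms line up only if an Anathema participant starts at once and never runs over.

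**Step 3. Let the stated rules act.** Write

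T3 (weeks from randomization) = s + 8 + 4r + 5v

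where s is the delay before access, r is the review time at each of the 4 transitions between 5 modules, and v is the overrun per module. The document gives only r, as up to 24 hours (1/7 week), for the guided and blended models. It gives no figure for s or v, so the values below are assumptions.

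| Case | s | r | v | T3 (week) |
|---|---|---|---|---|
| Nominal | 0 | 0 | 0 | 8.0 |
| Stated reviews at their limit | 0 | 1/7 | 0 | 8 + 0.57 = 8.6 |
| Self-guided, assumed small overrun | 0 | 0 | 0.25 | 8 + 1.25 = 9.25 |
| Guided or blended, assumed moderate slippage | 1 | 1/7 | 0.25 | 1 + 8 + 0.57 + 1.25 = 10.8 |
| Guided or blended, assumed large slippage | 2 | 1/7 | 1 | 2 + 8 + 0.57 + 5 = 15.6 |

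Only the first two rows rest on figures in the document. The second treats the full 24 hours as added time at every transition, so it is an upper limit for that source. The other rows show how quickly delay accumulates; they are not forecasts.

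**Step 4. Follow three kinds of participant through the text.**

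- *Finishes on schedule:* posttest at about week 8, level with the control re-assessment.
- *Withdraws or is dropped:* Discontinuation of Participation provides a final assessment if the participant agrees, at no stated time.
- *Stays in the trial but does not finish:* no posttest time is stated.

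**Step 5. Look for the control posttest.** The text gives no midtest or posttest time for controls. The assessment before access is described as an eligibility check. That it also serves as the control posttest is a reasonable inference, but it is not stated.

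**The case against.** The case on the other side is substantial, and much of it stands.

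- **The clocks agree on paper.** The program is planned for 8 weeks, and Study Intervention and TAU equates finishing it with about 8 weeks from baseline. A reader might infer that the plan measures the arms at different times. It does not say so; unequal timing is something the completion rule permits.
- **Non-finishers are not shut out.** A reader might infer that they have no posttest by rule. Discontinuation of Participation offers a final assessment to those who withdraw or are dropped, and Table 2 counts posttest completion among everyone who started baseline. What remains is narrower: neither place sets a time for someone who stalls without withdrawing.
- **A finishers-only analysis is not planned.** One could assume a non-finisher share and a gain among finishers and derive a percentage overstatement. All the inputs would be invented, and the Analysis section plans intention to treat with mixed models, which can use midtest data. That helps if missingness depends only on observed data. It does not repair unequal timing.
- **Posttest at week 5 is not supported.** Five modules at about one week each might suggest it, but Table 1 gives the third module weeks 3-6.
- **Selection of usability and acceptability scores is not shown.** The Measures section sets no time for those scales; only the interviews are described as postintervention.
- **Detail may lie elsewhere.** Figure 1 is not shown, and visit windows are often left to the full protocol. This is a fair caution. Even so, the completion trigger is stated text, and any calendar weeks given elsewhere would have to be reconciled with it.
- **Efficacy is secondary in a pilot.** This lowers the priority of the point without removing it.

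**Conclusion.** The point holds in a limited form. Posttest in the Anathema arm depends on adherence after randomization, while control re-assessment and access follow the calendar. They coincide at 8 weeks only when nothing slips, and the plan leaves no slack. Slower participants can therefore be measured after controls have crossed over, and participants who neither finish nor withdraw have no stated posttest time.

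The document's own figures support a shift of up to about 0.6 weeks from reviews alone. Anything larger rests on assumed start delays and overruns. The actual gap between arms, the number of participants affected and the resulting bias cannot be determined from the document. This is a worthwhile, inexpensive improvement to a stated rule; it is not a flaw that invalidates the pilot.

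**What to change.** 1. Set midtest and posttest at common calendar times from randomization in both arms, for example weeks 4 and 8, and send them to everyone randomized whatever their module progress.
2. State that the waiting-list assessment completed before access opens is the control posttest, as well as the eligibility check.
3. Use randomization as the single anchor in both Study Intervention and TAU and Enrollment and Randomization.
4. If an end-of-program questionnaire is wanted for slower participants, keep it as an additional, descriptive measure.
5. While editing, align the time-point labels: Table 2 calls midtest and posttest T1 and T2, whereas the delivery section calls them T2 and T3.

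Module pacing and the psychologists' decisions need not change. The cost is protocol wording and survey trigger dates. The article reports 49 participants randomized and recruitment ongoing, so the change would help only those not yet assessed. The downside is that some slower participants will be assessed before finishing, so the estimated effect may be slightly smaller.

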#### Discontinuation of Participation

Participants may withdraw from the study at any time and for any reason, without any consequences, or be dropped from the study by the research team if a severe aggravation of baseline measures occurs. In this case, the participant will be referred to psychology services at study sites or specialized resources in the community. The main reason for withdrawal will be registered, and a final assessment will be performed whenever the participant agrees with it. Participants who are lost to follow-up may be replaced to ensure a balanced number of participants in each study arm.

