### Measures

#### Primary Outcome Measures

The primary outcomes in this study are the acceptability, usability, and feasibility of Anathema. To assess Anathema’s acceptability, participants will self-report on the appropriateness and usefulness of the intervention’s content, length, usability, and service delivery model, using a self-developed 5-point Likert scale and the System Usability Scale [51].

Anathema’s feasibility-specific measures include recruitment, randomization, retention, and adherence rates (Table 2). Postintervention semistructured interviews will also be conducted to gather further data on Anathema’s usefulness, usability, and feasibility, as perceived by participants.

**Table 2 table2:** Primary outcome measures.

Outcome	Metrics
Acceptability	Self-developed 5-point Likert scale assessing the appropriateness and usefulness of the intervention’s content, length, usability, and service delivery model Postintervention semistructured interviews
Usability	System Usability Scale [51]
Feasibility	Recruitment: Number of participants screened per week Number of screening failures Number of participants enrolled per week Proportion of recruited participants opting to enroll Randomization: Proportion of eligible participants who access Anathema following randomization ‎Proportion of eligible participants who complete at least one module of Anathema Retention: Proportion of participants who complete T0 (baseline) measures Condition-specific completion rates following randomization (completion is defined as ≥50% of modules accessed at least once) ‎Proportion of participants initiating baseline measures who complete T1 (midtest) and T2 (posttest) measures Adherence: Proportion of participant dropouts from each intervention condition Proportion of participant withdrawals from the study Postintervention semistructured interviews

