#### Screening and Baseline Assessments

Screening and baseline assessments will be conducted by certified psychologists or psychology students supervised by the study team. The abovementioned outcome measures will be used for this purpose (Table 3). Participants fulfilling the eligibility criteria for the study will then be further assessed via a diagnostic interview. The Mini-International Neuropsychiatric Interview (MINI) [52] will structure this process. Participants with severe mental disorders will be referred to psychology departments at study sites or community mental health services.

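### Severe worsening can end study participation, not only the program, so later scores can be lost because of the outcome; the effect is small, its direction is unknown, and the fix is cheap

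*Protocol article*

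**What the plan says.** All references are to the protocol article.

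- **Discontinuation of Participation** lets a participant leave voluntarily "or be dropped from the study by the research team if a severe aggravation of baseline measures occurs". The participant is then referred to psychology services, the main reason is registered, and "a final assessment will be performed whenever the participant agrees with it". That assessment is not tied to the posttest date.
- **Screening and Baseline Assessments** identifies the baseline measures: "The abovementioned outcome measures will be used for this purpose (Table 3"). Table 3 lists the secondary outcome measures.
- **Study Intervention Delivery and Assessment** schedules outcome assessment at midtest and posttest.
- **Study Intervention and TAU** tells waiting-list participants that they are "free to access any form of support during the study and encouraged to seek professional help in case they experience symptomatic deterioration".
- **Enrollment and Randomization** gives the waiting list access to the program at about 8 weeks, "after being submitted to a second baseline assessment to confirm their eligibility for the study".
- **Table 2** counts as retention the share of "participants initiating baseline measures who complete T1 (midtest) and T2 (posttest) measures", and lists under adherence the "Proportion of participant dropouts from each intervention condition" separately from withdrawals from the study.
- **Analysis** specifies intention to treat with mixed models for the secondary outcomes, and the Jacobson-Truax method for clinical significance.

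**The concern.** The rule makes continued participation depend on the outcome. A person whose scores worsen severely can be removed by a team that is not blinded. After that, the article foresees one assessment, and only with the participant's agreement. Nothing shown says that scheduled visits continue.

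Three results could be touched: the between-arm contrast in the mixed model, the count of participants who deteriorate, and retention, which is a primary feasibility outcome. An analysis plan can model missing scores, but it cannot recover scores that were never collected.

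Protecting the participant does not require this. Referral can go ahead while questionnaires continue, and the waiting-list text already allows outside help during the study.

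**Working it through.** The article gives no removal rate, correlation or effect size, so there is no planned figure to reproduce. Everything below marked as assumed is an assumption, shown as a range.

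**1. Scale.** The article expects at least 30 participants per target group, or about 15 per arm if the split is even. The 95% CI half-width on a standardised difference is 1.96 × √(2/15) = 1.96 × 0.365 = 0.72 SD.

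**2. Mixed model.** This is a large simulation with 800,000 per arm.
- Assumed scores: baseline, midtest, a between-visit point and posttest, each with SD 1 and equal correlation 0.4, 0.6 or 0.8; higher is better.
- Assumed true effect: d = 0, 0.3 or 0.5 at posttest, with 0.5d at midtest and 0.75d between visits.
- Assumed trigger: a fall from baseline beyond a threshold that 5%, 10% or 15% of controls meet.
- Estimate: the posttest contrast under missing at random, given baseline and midtest.

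Bias in SD, where plus favours Anathema and no removed participant gives a final assessment:

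| Trigger | Who is removed | True d | Bias |
|---|---|---|---|
| Scored at midtest | any | any | 0.00 |
| Unscored, between visits | both arms equally | 0 | 0.00 |
| Unscored, between visits | both arms equally | 0.5 | about -0.01 to -0.03 |
| Unscored, between visits | Anathema arm only | 0 | about +0.02 to +0.05 |
| Posttest score itself (bound) | both arms equally | 0.5 | down to -0.11 |
| Posttest score itself (bound) | Anathema arm only | 0 | up to +0.21 |

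The first row is zero because loss then depends only on scores that the model contains. With no true effect, removal in the waiting list only mirrors the Anathema-only rows with the sign reversed. If half of those removed give a final assessment, the bias is roughly halved. A separate check used somewhat different assumptions (about 2.5-9% removed per affected arm, midtest score absent from the model). It gave at most about ±0.06, and about 0 with the midtest score on file.

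**3. Jacobson-Truax deterioration.** Let q be the true deterioration rate, s the share of deteriorated participants who are removed, and f the share of those removed who have a usable score.

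Observed rate = q(1 - s + sf) / (1 - sq + sqf). With q = 0.10 (assumed):
- s = 0.5, f = 0: 0.050/0.950 = 5.3%
- s = 0.5, f = 0.5: 0.075/0.975 = 7.7%
- s = 1, f = 0: 0%
- s = 1, f = 0.5: 0.050/0.950 = 5.3%
- f = 1: 10%, the true rate

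**4. Retention.** Removing 5-15% of 30 is 1.5 to 4.5 people. That takes up to 5-15 points off posttest completion if they leave before posttest without a final assessment. For comparison, the 95% CI half-width at an assumed 80% retention is 1.96 × √(0.8 × 0.2/30) = 14 points.

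**The case against.** The best counter-argument concerns where the trigger is seen. If it is a Table 3 score, someone must have administered a Table 3 measure. The article describes this only at midtest, posttest, the waiting-list second baseline and the final assessment. A midtest trigger is on file and gives no bias; at posttest nothing remains to be lost. The only textual route to a between-visit trigger is the psychologists' review after each module in the guided and blended models. Its stated consequence concerns moving on in the program, not leaving the study, and the self-guided group has no such review. This stands, and it is why the realistic bias is small.

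Safeguards also exist: the registered reason, the conditional final assessment, the mixed model, and Table 2's separate lines for dropouts and withdrawals. They limit the problem but do not remove it, because none of them keeps the scheduled assessments going.

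It could also be said that a journal article condenses such rules. But this is a stated rule with a stated object, the study; the point does not rest on a missing threshold or other detail.

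A reader might infer more than the text supports:
- **That removed participants leave the intention-to-treat analysis.** No text says so; the issue is only that their later scores may not exist.
- **That the rule favours Anathema.** It names no arm. Closer review of guided and blended participants could push that way, but an equal rule with a working program pushes the other way.
- **That the bias reaches -0.11 or +0.21 SD.** Those bounds need the trigger to be the posttest score itself and no final assessments; +0.21 also needs removals in the Anathema arm only.
- **That retention is biased.** Removal under the trial's own safety rule is a real feasibility result, and the recorded reason lets it be told apart.

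**Conclusion.** The point holds as a minor one. As written, the rule can lose midtest or posttest scores because of the outcome, and no later analysis can restore them.

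The effect on the mixed model is nil if the triggering score is recorded at an analysed visit. For an unscored between-visit trigger it is about -0.03 to +0.05 SD, for removals in both arms equally or in the Anathema arm only. The direction is not established, and the size is small beside the 0.72 SD half-width. These estimates are secondary and preliminary.

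The clearest loss is in the deterioration count: an assumed true 10% would be seen as 5.3% if half of those who deteriorate are removed with no usable score. The 0% case needs all of them removed and none with a usable score. Retention falls by the number removed, but the figure is genuine.

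The trigger rate, correlations, effect sizes and recovery shares are all assumed.

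**What to change.** In Discontinuation of Participation, replace removal from the study with stopping the program. For waiting-list participants, defer program access instead; the second baseline assessment is the natural point for that decision. Then:

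- keep the referral as it stands;
- invite these participants to all remaining scheduled assessments in their assigned arm unless they withdraw consent;
- record the triggering measure, score and date so that the analysis can use them, including for the clinical-significance classification on that measure when no later score exists;
- show team-initiated stops separately by arm within the existing Table 2 dropout figures.

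The cost is amended wording and a few more questionnaires for an assumed 1 to 5 people per target group. Those people will be distressed, so the invitation should be easy to decline.
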